### This Study and Objectives

Globally, pediatric palliative care interventions predominantly emphasize the stages of grief and psychological tasks that grieving parents must accomplish after their child’s death [22], and in Singapore, there is no known empirically tested intervention to provide psychoemotional support and psychoeducational resources to parents of children with chronic life-threatening illnesses. Singapore is a leading nation in digital readiness, smartphone utilization for communication is ingrained into the everyday life of its people [44], and web-based intervention services for improving well-being have been welcomed by the Singaporean community [45,46]. Hence, it is reasonable to propose that web-based solutions are vitally useful for enhancing pediatric palliative care and parental bereavement support services. Furthermore, in view of the fact that Asian family caregivers can be uncomfortable with explicit emotional expression even during times of loss and separation [47], a web-based platform and the relative anonymity it offers to participants [43] would be appropriate for an Asian population.

The research team of this study integrated the aforementioned elements necessary for a preloss intervention for parents of children with chronic life-threatening illnesses and conceived a Narrative e-Writing Intervention (NeW-I) to address the gap in pediatric palliative care delivery and research in the local context. NeW-I is a novel web-based, therapist-facilitated, strength-focused, and meaning-oriented intervention designed to provide direct service to parents of children with chronic life-threatening illnesses. The development and evaluation of NeW-I is guided by the Medical Research Council Framework for the Development and Evaluation of Complex Interventions, which is widely recognized in the design and evaluation of complex interventions to improve health outcomes [48,49]. NeW-I is also inspired by the meaning reconstruction model [50], the narrative approach to anticipatory grief [51], dignity therapy [31,32], family dignity intervention for holistic end-of-life care [33], and the findings of a recent investigation on Asian parental bereavement experience of child loss by our research team [13,14].

The overarching goal of the novel NeW-I intervention model is to provide an accessible platform for parent caregivers to reflect on their experiences of caring for a child with a chronic life-threatening illness from a new perspective (ie, new eye) as well as to create a renewed sense of self-understanding and empowered identity in the context of their experience (ie, new I). The specific research objectives are three-fold: (1) to develop a standardized protocol for a cultural-specific and meaning-oriented NeW-I for anticipatory grief and bereavement support for parent caregivers of children with chronic life-threatening illnesses and eventual death; (2) to evaluate the efficacy of NeW-I in enhancing quality of life, spiritual well-being, hope, and social support as well as decreasing caregiver burden, depressive symptoms, and risk of complicated grief among parent caregivers; and (3) to examine the challenges and pitfalls in the design and implementation of NeW-I through an integrated feasibility and acceptability study for informing large-scale implementation of the intervention.

## Methods

### Study Design and Hypotheses

This study utilizes an open-label randomized controlled trial design comprising 2 groups: (1) an intervention group (structured NeW-I protocol) and (2) a control group (journaling activity unrelated to their child’s illness). It is hypothesized that intervention participants who successfully complete NeW-I will experience an enhanced quality of life, spiritual well-being, sense of hope, and perceived social support and decreased depressive symptoms, subjective caregiver burden, and risk of complicated grief as compared with control participants. It is also hypothesized that NeW-I is deemed as an accessible and user-friendly service by participants.

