### Intervention and Control Groups

Both intervention and control group participants follow the procedures described in Figure 2. There are 4 weekly sessions of writing. A template has been provided to ensure that the participants’ writings tie in with the session objectives. To improve participants’ adherence to the study protocol, they receive an automated notification on their phone app and email each time a fresh writing session becomes available to them. Participants were assured of anonymity and confidentiality of their writing to encourage open and honest self-expression. The structured writing for each session requires 15 to 30 min, as exposure and time to process ideas through written disclosure over at least three sessions of 15 min each can produce effective outcomes [57].

For the intervention group participants, each weekly session has a unique objective (Table 2). Briefly, in week 1, participants reflect on the demands of caring for a child with a chronic life-threatening illness and the means to cope with these challenges. In week 2, participants consider avenues where they could seek more information about their child’s illness and resources for caregiving. In week 3, participants examine the sources of support that they have within their network of family and friends. In week 4, participants explore how they (and their children) could rise above illness-related challenges and live their lives as fully as possible.

For control group participants, the objective is consistent across the 4 weeks, that is, participants engage in a weekly writing session that is unrelated to their child’s illness and allows them to experience the therapeutic benefits of narrative writing (Table 3).

**Table 2 table2:** Content and questions for reflective writing for intervention group.

Session structure	Week 1	Week 2	Week 3	Week 4
Objective	To provide participants with a platform to reflect on the emotional, practical, and financial demands of caring for a child with a chronic life-threatening illness and the means to cope with these challenges.	To explore avenues where participants can seek more information about their child’s illness and resources for caregiving.	To explore the sources of support that participants have within their close network of family and friends.	To explore how participants (and their children) can rise above illness-related challenges and live their lives as fully as possible.

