Questions for reflective writing	Tell us a little about your child and what you love about him or her. Tell us about the challenges that you have encountered when caring for your child. What has been your biggest challenge so far? How have you coped with it? What are three things that have helped you cope in your caregiving journey?	How satisfied are you with the knowledge and information that you have about your child’s condition? What has been helpful in providing you with the knowledge and information? What are some forms of support that have been helpful for you in providing quality care to your child? How were these forms of support helpful? What would help you to feel more competent as your child’s caregiver? What is one thing you could do to make that difference?	Tell us about some people who have been helpful or supportive in your caregiving journey. How have they helped you to cope during difficult times? On a scale of 1 to 10, with 1 being “Not at All” and 10 being “Very Much,” how satisfied are you with your spousal relationship? (Please omit this question if it does not apply to you.) What might make that score a little higher? What are some things that others could do for you that could further help you in your caregiving journey?	Tell us what you love best about your child. What quality about him or her makes you proud? What would a good day for your child look like right now? What makes it a good day? Tell us about an enjoyable moment with your child. What are some things you can do to make an enjoyable moment happen?

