Counseling goals	To affirm the strengths that have helped participants to survive and thrive. To provide psychoeducation about local social welfare organizations that can provide them with support.	To acknowledge participants’ efforts to seek power and control over their seemingly uncontrollable lives through illness literacy. To provide psychoeducation about sources for seeking more information about their child’s illness, treatment options, and resources for caregiving.	To reframe that they are indeed blessed to have the support of their spouse or family or friends to help them to cope with this challenging period. To reframe participants’ sharing from sessions 1, 2, and 3 by taking the semantic content as it is but providing an alternative viewpoint of perceiving the situation.	To assist participants (and their children) in building meaningful and cherished memories through reflecting on achievements and fulfillment of dreams. To examine ways in which participants can enhance quality of life in their child’s final days.

**Table 3 table3:** Content and questions for reflective writing for control group.

Session structure	Week 1	Week 2	Week 3	Week 4
Questions for reflective writing	This week, we’d love to know a little bit about you. Tell us what an average day in your life looks like. Feel free to share with us any and every detail that you find comfortable to talk about!	This week, we’d like to know about what has the past week been like for you? Feel free to share with us in as much detail as you like!	This week, we’d like to know what is the biggest challenge (e.g. emotional, financial, practical etc.) that you are facing right now? Do feel free to add on anything else about this challenge that you would like us to know!	This week, we’d like to know what you find most comforting right now (e.g. family, relationships, work, hobbies and other activities etc.). Tell us about what makes this thing comforting for you?

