## Discussion

### Research Synopsis and Implications

NeW-I is a first-of-its-kind, web-based, therapist-facilitated, strength-focused, and meaning-oriented intervention for parents of children with chronic life-threatening illnesses, thereby filling in a critical service gap in local pediatric palliative care. Through an open-label randomized control trial, the efficacy of NeW-I for improving such parents’ quality of life, spiritual well-being, hope, and social support and decreasing depressive symptoms, caregiver burden, and risk of complicated grief is investigated across 5 time points. It is expected that parents who successfully complete the structured NeW-I intervention protocol will experience enhanced quality of life, spiritual well-being, sense of hope, and perceived social support and decreased depressive symptoms, subjective caregiver burden, and risk of complicated grief as compared with parents who engage in a journaling activity unrelated to their child’s illness (control group). It is also expected that parents will find NeW-I to be an accessible and user-friendly service.

In addition to improving the psychosociospiritual well-being of parent caregivers, this study creates opportunities for (1) a longitudinal assessment of the mental states of 36 parents (ie, control group) to obtain a naturalistic trajectory of anticipatory grief, (2) an evaluation of the extent to which the intervention is successful in improving the mental well-being of 36 parents (ie, intervention group), and (3) an evaluation of the extent to which these potential positive effects are sustained over time. The findings will inform the development of a full-scale NeW-I protocol that will be disseminated via research papers and presentations. This will form the foundation for further empirical research to test the effectiveness, acceptability, and feasibility of NeW-I in Singapore and in other Asian communities around the world.

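### The control is an active writing arm: it cannot show a naturalistic course of grief, and its prompts do not secure writing unrelated to the child's illness

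*Protocol article*

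**What the plan says.** The protocol article describes the control arm in three places.

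- **Study Design and Hypotheses:** the comparator is "a control group (journaling activity unrelated to their child’s illness".
- **Intervention and Control Groups:** controls write once a week on something "unrelated to their child’s illness and allows them to experience the therapeutic benefits of narrative writing". The same section gives four weekly sessions of 15 to 30 minutes. It justifies this by stating that written disclosure over three or more 15-minute sessions can be effective.
- **Research Synopsis and Implications:** the comparator is again described as journaling unrelated to the illness. Among the opportunities the study creates is a "longitudinal assessment of the mental states of 36 parents (ie, control group) to obtain a naturalistic trajectory of anticipatory grief".

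Table 3 prints the control prompts. Week 1 asks about an average day and week 2 about the past week. Week 3 asks "what is the biggest challenge (e.g. emotional, financial, practical etc.) that you are facing right now". Week 4 asks "what you find most comforting right now (e.g. family, relationships, work, hobbies and other activities etc". In Table 2, the intervention's week 1 objective concerns the emotional, practical and financial demands of caregiving, and its questions include "What has been your biggest challenge so far? How have you coped with it".

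**The concern.** Two statements about the control arm do not match the arm as designed.

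The first is a stated use. A naturalistic course is what happens without an intervention directed at the outcome, and this arm receives an activity that the article itself regards as therapeutic.

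The second is a stated property. The writing is said to be unrelated to the child's illness, but at least one prompt invites a topic that the intervention arm also covers, in closely similar terms.

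What is at stake is interpretation. The second research objective is to evaluate the efficacy of NeW-I, and the findings are to inform a full-scale protocol. The between-group difference estimates what NeW-I adds to structured writing on partly shared themes. The control curve describes parents who have done that writing. Reported under the present description, either could be taken for something it is not.

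**Working it through.** The point is textual. The one related figure in the plan is the size of the arm, and it reproduces: 25 / (1 − 0.3) = 35.7, rounded up to 36 per group, or 72 in total. Nothing below changes it.

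**Step 1: is the control course naturalistic?** Set the article's writing rationale beside what controls receive.

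| Item | Source | Value |
|---|---|---|
| Writing said to be capable of effect | Intervention and Control Groups | at least 3 × 15 min = 45 min |
| Writing scheduled for controls | Same section | 4 × 15 = 60 min to 4 × 30 = 120 min |
| Purpose of control writing | Same section | "allows them to experience the therapeutic benefits of narrative writing" |
| Assessments | Quantitative Assessments | baseline; end of protocol; 1, 3 and 6 months later |

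Controls are scheduled for more writing than the amount the article calls sufficient, with benefit as a stated purpose. Only baseline precedes the writing, and the other four of the five assessments follow it. No part of the control curve after baseline is free of the activity.

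**Step 2: do the prompts secure writing unrelated to the illness?** Compare Table 3 with Table 2.

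| Control week | Topic | Nearest intervention content | Overlap |
|---|---|---|---|
| 1 | an average day | none specific | neutral |
| 2 | the past week | none specific | neutral |
| 3 | biggest current challenge: emotional, financial, practical | week 1: emotional, practical and financial demands; biggest challenge so far | close |
| 4 | what is most comforting; examples are family, relationships, work, hobbies | week 1: three things that helped coping; week 3: support from family and friends | partial |

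Week 3 uses the same three domains and the same central question. Week 4 shares family and relationships, but its work and hobby examples point elsewhere. No control prompt names the child, the illness or caregiving, and none asks the parent to leave them out. The article's Background describes practical and financial burden and strained relationships as part of these parents' lives. An answer to the week 3 prompt could therefore readily concern the illness. How often it does is unknown.

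**Step 3: how much narrower is the contrast?** This would need the share of any NeW-I benefit that control writing also delivers. The article gives no such figure and nothing from which to derive one, so no estimate is made.

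**The case against.** The strongest reply is that the article is open about using a writing control, and that such a control is legitimate. Writing can be unrelated to the illness and still therapeutic; the two properties stand in one sentence and do not conflict. Two of the four control weeks are neutral, week 4 overlaps only in part, and no control prompt mentions the child or the illness. The intervention keeps content of its own: illness information, caregiving resources, and counseling goals such as affirmation, reframing and psychoeducation. Table 3 has no counseling row. A template is said to tie the writing to each session's objective, and Figure 2, which is not shown here, may tell controls more. The naturalistic phrase appears once, in the Discussion, and drives no hypothesis, endpoint or analysis.

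Most of this stands, and it limits the point. The contrast is narrowed at most, not removed. It does not rescue the naturalistic claim, which conflicts with the arm's stated purpose. Nor does it make the week 3 prompt secure the property claimed for the arm. The template does not settle the matter either, because the prompts in Table 3 are the only session content the article prints for controls.

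A reader might infer that the true effect is diluted by some definite fraction and that a later trial would have to grow accordingly. The documents do not support this. They give no dilution, and the effect size of 0.2 under Sample Size Calculation is not tied to an inert comparator. If a later trial kept this comparator, planning it on the contrast with active writing would be correct. A reader might also infer that the control prompts must be replaced in the full-scale trial. That is a design preference, not a consequence of the text.

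**Conclusion.** The point holds as one of description and interpretation, and it should be corrected. The control arm receives four writing sessions meant to help, so it cannot supply a naturalistic trajectory of anticipatory grief. Its prompts do not secure writing unrelated to the child's illness, chiefly because of week 3 and in part because of week 4. The contrast may be narrowed by an amount that cannot be estimated from the documents.

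The first conclusion rests only on the article's own account of the arm's purpose and schedule. The second rests on the prompts as printed and assumes that Figure 2 does not instruct controls to keep the illness out of their writing. The possible narrowing rests on a further assumption, plausible but not stated in the documents, that some controls write about the illness or benefit from writing on shared themes.

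It would go too far to say that the article plans to treat the control curve as untreated, or to size the main trial on it. It says neither. Sample size, endpoints and the planned mixed model are not affected.

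**What to change.** 1. Wherever the comparator is described (Study Design and Hypotheses, Intervention and Control Groups, Research Synopsis and Implications), call it an active writing control whose prompts do not ask about the child's illness. First reconcile that wording with what controls receive under Figure 2, including any therapist feedback; the section on acceptability and feasibility refers to feedback to participants without naming the arm.
2. Delete the naturalistic-trajectory claim, and do not use the control curve as an untreated course.
3. State the conclusion as the added effect of NeW-I over active writing.
4. If consent and the assurance of anonymity and confidentiality allow, code each control text yes or no for illness content and report the proportion. This would show how far the writing was in fact unrelated to the illness.

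Items 1 to 3 cost only wording and leave the running trial unchanged. Item 4 costs a small amount of coding work and a check that it is permitted. The downside is a more modest claim about the control arm.

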### Sample

The sample comprises 72 individual parents of varying ethnicity in Singapore (N=72). Where both parents of a child participate in the study, their group allocation is randomly determined, and assessments are completed by both parents independently. To be eligible for participation in this study, the individual must be a parent whose child has been diagnosed with a chronic life-threatening illness and has a prognosis of more than 3 months at the time of enrollment. For the purpose of this study, a *child* has been defined as children and young persons between the ages of 0 and 19 years [52]. The individual must be able to speak, read, and write in English and provide informed consent. Individuals are excluded from this study if they are suffering from severe depressive symptoms and psychological distress, as identified by 2 screening tools. Specifically, to protect participants’ well-being during the pilot testing of NeW-I, those who do not meet the stated cutoff scores of the Patient Health Questionnaire – 9 (PHQ-9; >19) and Kessler psychological distress scale (K-10; >29) are excluded, as formal treatment and therapy would be more beneficial [53,54]. Additionally, if participants cease to meet the inclusion criteria during the study (eg, due to their child’s untimely death), they are excluded from the study and provided with alternative resources for psychosocial support. However, the data that have been collected until the time of their participation will be kept and analyzed so that a complete and comprehensive evaluation of the study will be possible.

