### Sample Size Calculation

For a main trial designed with 90% power and two-sided significance level of at least .05, a pilot sample size of 25 per arm is needed to detect a small effect size of 0.2 in the primary outcome measure [55]. A meta-analysis suggested that many high-quality psychotherapy studies (high quality studies defined by a proficiently trained therapist, treatment integrity, N>50) on the treatment of depression have a mean effect size of 0.22 [56]. Allowing for an attrition rate of 30% at follow-up (a larger estimate due to end-of-life context), the sample size must be inflated by a factor of 1/(1−0.3)=1.43. Therefore, the minimum sample size required for this study was 72 or 36 in each group.

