Following this, participants are directed to a screening page where participants complete the PHQ-9 and the K-10. Those who pass the screening assessments receive confirmation of study participation and are requested to wait for a phone call from the research team. Those who do not pass the screening assessments are thanked for their time and provided with resources for psychosocial support. Individuals who pass the screening assessments receive a phone call from the NeW-I team as a means of identity checking. Following this, participants complete baseline measures (time point 1 assessment). This is followed by a random allocation of participants to either the intervention group or the control group, which is performed via the NeW-I platform using computer-generated random numbers. Participants are then directed to the first writing session. Participants have the option to choose to begin the first writing session immediately or delay for a maximum of 3 days. The day on which participants begin their first writing session is day 1 of week 1. Participants who do not begin their first writing session within 3 days are excluded from the study. However, a concession period of 7 days is given to participants who have a genuine reason for their inability to adhere to the protocol (such as unexpected changes in their child’s health condition) and have expressed keen interest in participating in the study. A similar concession period of 7 days is also maintained for participants who are unable to adhere to the study protocol in weeks 2, 3, and 4 (such that each participant can only be given 1 concession during the entire duration of their study participation). Detailed study procedures are described in Figure 2.

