### Data Analysis

#### Quantitative Data

The statistical analysis plan for the quantitative data in this study was designed according to the Consolidated Standards of Reporting Trials guidelines [64] and recommendations made by Gamble et al [65] for clinical trials. Quantitative parameters will be presented as mean (SD) or median (IQR), and categorical variables will be presented as numbers and proportions. The internal consistency of psychometric scales will be assessed using Cronbach alpha. To compare the primary quantitative outcome (KQOL) and secondary quantitative outcomes (FACIT-Sp-12, HHI, PHQ-9, BSFC-s, ISS, and BGQ) between the intervention and control groups over time (time point 1 to time point 5, with time point 2 being the primary time point of comparison), multilevel mixed-effect regression analysis will be used with time as a random effect. All demographic and other relevant covariates measured at baseline will be adjusted in the model. Mixed models allow us to include all available data in the presence of dropouts occurring into the analysis [66]. Individual multivariable models will be constructed for each outcome to estimate the effect sizes and corresponding CIs. Clinically meaningful interactions will also be checked and included in the model if *P*<.10. Marginal effects will be used to predict mean outcome scores for the intervention and control groups. For this study, a two-sided significance level of at least .05 will be considered a statistically significant finding. All analyses will be conducted using Statistical Package for the Social Sciences (SPSS) (version 22.0; IBM Corp) and Stata (version 15.1; StataCorp) statistical software.

The intention-to-treat principle will be followed in the data analysis. However, an additional sensitivity analysis will be conducted to handle missing data during the analysis, where fully conditional multiple imputation with *n (% missing)* imputations and 1000 iterations using the Markov Chain Monte Carlo method will be used [67]. Model summary estimates will be calculated based on the Rubin rule [68].

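### Both parents of one child may enrol, but the outcome model names no family level, so its standard errors depend on how couples happen to fall across the arms

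*Protocol article*

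**What the plan says.** The Sample section of the protocol article counts 72 individual parents and provides for couples: "Where both parents of a child participate in the study, their group allocation is randomly determined, and assessments are completed by both parents independently". It does not say whether the two parents are randomised separately or as a unit.

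The App and Intervention Procedure section describes the mechanism after the baseline assessment: "This is followed by a random allocation of participants to either the intervention group or the control group". The platform does this with computer-generated random numbers. No rule, block or stratum for couples is named.

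The Sample Size Calculation section starts from 25 per arm and allows only for attrition: "the sample size must be inflated by a factor of 1/(1−0.3)=1.43".

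The Quantitative Data section says that "multilevel mixed-effect regression analysis will be used with time as a random effect", and on covariates that "All demographic and other relevant covariates measured at baseline will be adjusted in the model". No couple, family or child level appears. Time point 2 is the primary comparison.

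**The concern.** Two parents caring for the same seriously ill child are likely to resemble each other in quality of life, burden, grief and perceived support. The design lets such pairs in, and the model as described has no term for them. The error in the standard error then depends on where the pairs fall. Pairs in the same arm make the reported standard error too small. Pairs split across arms make it too large.

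Split pairs raise a second, separate issue. The trial is open label, and the week 3 intervention session deals with the spousal relationship and with family support (Intervention and Control Groups, Table 2). A control parent living with a NeW-I participant could benefit indirectly, which would pull the contrast toward zero. That matters because the pilot's findings are meant to inform a full-scale protocol.

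**Working it through.** **The plan's own figure.** 25/(1 − 0.3) = 35.7, rounded up to 36 per arm, so N = 72. This reproduces the stated size. It contains no allowance for couples.

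**Inputs that the documents do not give.**
- f, the share of participants enrolled as one of a pair. The only anchor is the team's earlier Singapore study of bereaved parents (Introduction, Parental Bereavement Trajectories of Child Loss): 6 couples, 13 mothers, 4 fathers and 2 primary parental figures. Counting each couple as two people and every other unit as one gives 12/(12 + 13 + 4 + 2) = 12/31 = 0.39. That is a different population, so it is indicative only. Range used: 0.39 to 0.50.
- ρ, the within-couple correlation. Assumed 0.3 to 0.5.
- c, the share of the NeW-I effect that reaches a control parent through a spouse. Assumed 25% to 50%.

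**Formulas, for a comparison at a single time point.**
- All couples in the same arm: DE = 1 + fρ.
- All couples split: DE = 1 − fρ.
- A given realised allocation: DE = 1 + 2ρ(S − D)/N, with S same-arm pairs and D split pairs.
- True type I error of an analysis that ignores pairs: 2[1 − Φ(1.96/√DE)].

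**Results for the two extremes.**

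| f | ρ | Same arm: DE | Type I error | Split: DE | Type I error |
|---|---|---|---|---|---|
| 0.39 | 0.3 | 1.12 | 6.4% | 0.88 | 3.7% |
| 0.39 | 0.5 | 1.19 | 7.3% | 0.81 | 2.9% |
| 0.50 | 0.3 | 1.15 | 6.8% | 0.85 | 3.4% |
| 0.50 | 0.5 | 1.25 | 8.0% | 0.75 | 2.4% |

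The true standard error is √DE times the reported one: about 1.06 to 1.12 times with couples in the same arm, and about 0.94 to 0.87 times with couples split.

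**Each parent randomised separately.** Same-arm and split pairs roughly cancel. In simulation (N = 72, two-sample t-test, 6,000 runs per setting, f from 0.25 to 1.0, ρ of 0.3 and 0.5), type I error was 0.044 to 0.051, so about nominal on average.

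A particular allocation need not balance. At f = 0.5 there are 18 pairs. If 12 share an arm and 6 are split, S − D = 6 and DE = 1 + 2ρ × 6/72, which is 1.05 at ρ = 0.3 and 1.08 at ρ = 0.5. Type I error is then 5.6% to 6.0%. With the numbers reversed, DE is 0.95 to 0.92 and type I error 4.4% to 4.1%.

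**Spillover under separate randomisation.** About half of the control parents in couples have a NeW-I spouse, so d = 0.20 × (1 − f × 0.5 × c). At f = 0.39:
- c = 25%: 0.20 × 0.952 = 0.190.
- c = 50%: 0.20 × 0.903 = 0.181.

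At 90% power and two-sided 0.05, a main trial needs 526 per arm for d = 0.20. Scaling by 1/0.952² and 1/0.903² gives about 581 and 645 per arm.

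**The case against.** The strongest reply is that the documents point to separate randomisation of each parent, and under that reading the naive error rate is close to 5% on average. This stands. A reader might infer that the reported confidence interval is wrong whichever way couples are allocated, or that inflated type I error and contamination apply together. Neither is supported: inflation needs couples concentrated in one arm, and contamination needs them split.

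It can also be said that the phrase about time is shorthand, since it names no participant intercept either, and that the full random-effect structure may sit in an analysis plan not shown. This stands in part. The article nowhere declares the 72 to be independent; that is inferred from the model as named. But the article itself admits couples and itself names the random effect, and the two do not fit together as written.

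A reader might further conclude that control spouses are directly exposed to NeW-I. They are not. Accounts are individual, writing is confidential, and control parents receive their own prompts. Any spillover is indirect, and its size is an assumption.

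Finally, giving the second parent the first parent's arm may look like the obvious remedy. In an open-label trial that parent could know the arm before enrolling, which loses allocation concealment. It would create the same-arm design effect and would change the rule during recruitment. It is a trade-off, and nothing in the documents requires it.

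**Conclusion.** The point holds as a mismatch between the design and the model: couples are admitted, the allocation rule for them is not stated clearly, and no family level is named. Within the assumed ranges for f and ρ, true type I error lies between about 2.4% (all couples split) and 8.0% (all in the same arm). Under the most natural reading it is near nominal on average. What remains then is a standard error that can be off for the allocation actually obtained, and some lost precision because the pairing is not used.

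Dilution from split couples is modest on these assumptions, from 0.20 to about 0.18 to 0.19. A reader might infer that 72 is too small because it carries no design effect. That is not shown for a pilot, and a larger size would follow only if couples were placed in the same arm.

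**What to change.** - In the Quantitative Data section, add a random intercept for family (child), with participant nested within family, to every outcome model. Family-clustered robust standard errors are an alternative.
- Report how many couples share an arm and how many are split.
- Add a sensitivity analysis using one parent per child, or one that excludes control parents whose spouse is in the NeW-I arm.
- In the Sample section, state whether the two parents of a child are randomised separately or together. The current allocation can stay as it is.

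Cost: one more variance component, which may be weakly estimated if couples are few, and slightly wider confidence intervals if couples mostly share an arm. The modelling and reporting changes need no change to recruitment or allocation, provided that parents of the same child can be linked in the data.
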